#### Laboratory analysis

2.6.3

In all participants, blood samples will be collected prior to each oral food challenge to measure total IgE (tIgE) and specific IgE (sIgE) antibodies to hen's egg white and ovomucoid (Gal d 1). Previous studies have demonstrated the value of assessing the sIgE/tIgE ratio as a predictor of OFC outcomes (28, 29).

In addition, a basophil activation test (BAT) will be performed prior to each OFC. As a functional assay, BAT has demonstrated greater accuracy than sIgE measurement alone in identifying baked and lightly cooked egg allergy. Krawiec et al. (29) found that BAT improves the predictive value for a positive OFC outcome with baked egg and reduces the number of OFCs in children aged 6 months to 15 years with suspected egg allergy.

Both sIgE/tIgE ratio and BAT may support the identification of children who are more likely to tolerate food allergens during OFC. However, its role in predicting response to OFC with baked egg remains to be fully established.

### Adherence

2.7

To systematically assess participant adherence and monitor the occurrence of anaphylactic events, parents will be instructed to meticulously document, on a daily basis, the quantity and frequency of at-home allergen administration during the final week preceding each OFC, as well as to record any suspected adverse reactions occurring at any time throughout the six-week interval between OFCs, using the Egg Ladder Monitoring Diary (developed by the study investigators, Additional File 2*****). This diary in paper form will be maintained throughout the six-week intervals between OFCs.

### Follow-up

2.8

Patients will be followed up by the research team to assess their ongoing tolerance and continued inclusion of egg in their diet at 6 weeks after completing the EL.

### Sample size justification

2.9

This study is designed as a randomized controlled trial (RCT) to compare the clinical effectiveness and safety of two versions of an egg ladder protocol: one with four steps and the other with five steps, in children with IgE-mediated hen's egg allergy.

A formal sample size calculation based on statistical power was not feasible due to the lack of standardized data regarding allergen content and clinical reactivity across different baked egg preparations used in oral food challenges. As noted in the existing literature, studies assessing the immunological and clinical progression through the egg ladder remain limited, and standardized endpoints have not yet been universally defined.

Therefore, this trial was informed by available clinical evidence and precedent from similar studies involving the milk ladder in cow's milk-allergic children. In particular, a comparable RCT evaluating the impact of introducing baked cow's milk on tolerance development included 84 children (42 per arm) and demonstrated sufficient power to detect clinically meaningful differences (14).

Moreover, a recent randomized trial by De Vlieger et al. (12), which evaluated short- vs. long-term guided gradual egg reintroduction in baked egg–tolerant children, also enrolled 78 children (39 per arm) and successfully identified significant differences in tolerance acquisition timelines.

Based on this evidence and our clinical experience, a total of 94 children (47 per group) will be recruited to allow for an anticipated 10% dropout rate, ensuring that at least 84 participants (42 per group) complete the trial. This sample size is considered both feasible and appropriate to meet the study objectives while allowing an initial exploration of clinical differences between the two egg ladder variants. This pilot trial will generate effect size estimates to inform future confirmatory studies and formal sample size calculations.

### Study duration and rationale

2.10

Based on evidence from the literature (30), a study duration of 36 months is considered sufficient to complete participant recruitment and implement the interventions across both study subpopulations.

### Outcomes

2.11

#### Primary outcome

2.11.1

The primary outcome is the percentage of children who acquire tolerance to soft-boiled hen's egg (almost raw hen's egg proteins), as determined by a negative OFC at the final step of the EL. Soft-boiled egg will be administered at the end of the observation period (18 or 24 weeks, depending on the assigned study arm).

The challenge dose will consist of 0.5–1 egg for children aged 1–3 years and 1 egg for those aged 4–5 years, corresponding to a maximum total of 6 g of hen's egg proteins. The outcome will be reported as a difference between two study arms.

#### Secondary outcomes

2.11.2

All secondary outcomes will be reported as a difference between two study arms.
The percentage of children with a negative OFC at each step of the EL protocol upon completion of the study's observation period (18 weeks and 24 weeks, depending on the study arm), calculated as the proportion of children tolerating the full planned dose for each step.The proportion of children who experience anaphylaxis during the observation period (18 or 24 weeks, depending on study arm), defined as reactions with severity grades 3–5 according to the updated 2023 WAO clinical criteria for anaphylaxis (27).The proportion of children with anaphylaxis (grades 3–5, per 2023 WAO criteria) who required epinephrine administration, categorized by:
○one or two doses of intramuscular epinephrine with a good clinical response (less severe reaction, grade 3),○more than 2 doses of intramuscular epinephrine,○lack of significant clinical improvement after two doses (severe reactions, grades 4–5),○measured during the observation period (18 or 24 weeks, depending on the study arm).The proportion of children who experienced systemic allergic reactions (SAR) of grades 1, 2, and 3 according to the 2023 WAO grading system, with specific reference to gastrointestinal symptoms:
○grade 1: includes nausea and/or mild abdominal pain without altered activity;○grade 2: persisting (≥20 min) and non-distractable abdominal pain and/or vomiting (not due to gag or taste aversion) and/or diarrhea;○grade 3: severe, persistent (≥20 min), intractable abdominal pain and/or vomiting (excluding retching or taste aversion) and/or diarrhea, assessed during each OFC measured during the observation period (18 or 24 weeks, depending on the study arm).In the subgroup of children with AD, changes in the total score of the oSCORAD index (26) will be assessed before and after each OFC. Any documented exacerbation of AD symptoms following OFC will be also recorded.Change in age-adjusted *z*-scores for weight and length/height, evaluated using the WHO growth charts (31), from baseline (prior to the first OFC) to the end of the observation period (18 or 24 weeks, depending on the study arm).Change in the total score of the FAQLQ-PF (24), at the end of the observation period (18 weeks and 24 weeks, depending on the study arm) from baseline.Mean difference in caregiver anxiety levels, measured by the Subjective Units of Distress Scale (SUDS) (25) prior to each OFC, between study groups at each time point.The proportion of children with full adherence to the intervention protocol, defined as consumption of at least one portion of a tolerated hen's egg proteins dose three times during last week of break in period, in the same form and quantity as tested during the OFC. Data will be collected through the Egg Ladder Monitoring Diary and assessed throughout each break in period (between the following steps of each ladder).

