**Methods:**

We will perform an open-label randomized trial with two-parallel arms in two departments if the same academic hospital. A total of 84 children with IgE-mediated HEA will be allocated in 1:1 ratio to introduce hen's egg allergy into their diet according to either 4-EL or 5-EL with 4-week break period between subsequent steps. Oral food challenge (OFC) with tested products at each subsequent step of the EL will be conducted in hospital settings. The primary outcome will be the percentage of children with tolerance to non-heated hen's egg proteins defined as non-allergic reaction to raw hen's egg (0.5–1 egg, depending on the age of the patient) during the last OFC; measured at the end of the 18-week observation period for the 4-EL and 24-week observation period for the 5-EL. Secondary outcomes will include the percentage of children with negative OFC to each EL step; the percentage of children with anaphylaxis (including the percentage of those who were treated with epinephrine); the percentage of children with exacerbation of atopic dermatitis; growth; compliance; and quality of life of the caregivers and parents anxiety about adverse events during their child's OFC.

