### Statistical analysis

2.19

Descriptive statistics will be used to summarize baseline characteristics. For continuous variables, comparisons between groups will be made using the Student's *t*-test, Mann–Whitney *U*-test or Wilcoxon signed rank test, depending on whether or not the variables are normally distributed. The appropriate statistical test will be employed to compare percentages, either the χ^2^ test or Fisher's exact test.

For continuous outcomes, the differences in means or medians (depending on the distribution of data), and for dichotomous outcomes, the relative risk (RR) and number needed to treat (NNT), all accompanied by a 95% CI, will be calculated. The difference between study groups will be considered statistically significant if the *p*-value is less than 0.05, if the 95% CI for RR does not include 1.0, or if the 95% CI for mean difference does not include 0. All statistical tests will be two-tailed and performed at the 5% level of significance.

An intention-to-treat (ITT) analysis including all randomised participants, regardless of protocol adherence or withdrawal, will be applied. A per-protocol analysis that includes all participants who finish the study according to the protocol will also be performed.

The number of missing data with reasons will be reported for each study arm, and compared qualitatively between groups, if feasible. Multiple imputation methods for missing data will be applied to address missing data, as recommended (34).

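### Epinephrine use reads most naturally as a share of children with anaphylaxis yet is to be compared between arms, so that comparison is not protected by randomisation; its categories can also overlap as printed

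*Protocol article*

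**What the plan says.** Section 2.11.2 (Secondary outcomes) of the protocol article lists anaphylaxis first, with no conditioning: "The proportion of children who experience anaphylaxis during the observation period (18 or 24 weeks, depending on study arm". The next outcome is "The proportion of children with anaphylaxis (grades 3–5, per 2023 WAO criteria) who required epinephrine administration, categorized by" three response groups:

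- "one or two doses of intramuscular epinephrine with a good clinical response (less severe reaction, grade 3"
- "more than 2 doses of intramuscular epinephrine"
- "lack of significant clinical improvement after two doses (severe reactions, grades 4–5"

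A fourth bullet gives only the time window. The section opens with a rule that covers all of these outcomes: "All secondary outcomes will be reported as a difference between two study arms".

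The abstract (Methods) describes the pair as "the percentage of children with anaphylaxis (including the percentage of those who were treated with epinephrine". Section 2.19 (Statistical analysis) adds: "An intention-to-treat (ITT) analysis including all randomised participants, regardless of protocol adherence or withdrawal, will be applied". It does not say how this applies to an outcome defined within children who had a reaction.

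**The concern.** Anaphylaxis happens after randomisation, and the two ladders may change both who has it and how severe it is. Sections 2.1 and 2.5 give the 4-step arm four challenges over 18 weeks, starting at 1.5 g of egg protein. The 5-step arm has five challenges over 24 weeks, starting at 0.75 g. Children with anaphylaxis in one arm therefore need not resemble those in the other. A relative risk or number needed to treat calculated within that group, as section 2.19 provides for dichotomous outcomes, is not a randomised contrast.

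Safety is part of the primary aim (section 2.1), and the results are meant to inform guideline groups. An arm with more anaphylaxis could show a smaller treated share and appear better on this line, although more of its randomised children received epinephrine.

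A second, smaller defect is that a child who does not improve after two doses and then receives a third fits both the second and the third response group. No rule says where that child is counted.

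**Working it through.** **Inputs from the protocol article.** Section 2.9 gives 94 children, 47 per arm, and 10% dropout to leave 84 completers. This reproduces: 84 / 0.9 = 93.3, rounded up to 94; 42 / 0.9 = 46.7, rounded up to 47. The article gives no rate for anaphylaxis or epinephrine use, so every rate and count below is an assumption for illustration.

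**Notation.** A = children with anaphylaxis in an arm; E = those of them given epinephrine; n = 47 randomised. The conditional share is E/A and the share per randomised child is E/n.

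**Can the direction differ?** Two sets of assumed counts:

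| | 4-step | 5-step | Arm that looks better |
|---|---|---|---|
| Set 1, E/A | 3/6 = 50% | 2/3 = 67% | 4-step |
| Set 1, E/n | 3/47 = 6.4% | 2/47 = 4.3% | 5-step |
| Set 2, E/A | 6/10 = 60% | 3/4 = 75% | 4-step (RR 0.80) |
| Set 2, E/n | 6/47 = 12.8% | 3/47 = 6.4% | 5-step (RR 2.0) |

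Fisher's exact p is 1.00 for both rows of set 1, and 1.00 and 0.49 for set 2. The table shows a conflict of direction, not evidence for either ladder.

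**When it reverses.** Let a be the anaphylaxis rate and c the treated share among cases. The two measures disagree in this direction when a(4-step)/a(5-step) > c(5-step)/c(4-step) > 1. In set 1, (6/47)/(3/47) = 2.0 and (2/3)/(3/6) = 1.33, so the condition holds. If the extra cases need no epinephrine it does not hold. For example, 2/6 against 2/3 gives 33% v 67% conditionally but 2/47 in both arms; the conditional figure then suggests a difference where the randomised comparison shows none.

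**How often.** Simulation of 200,000 trials at 47 per arm, with A binomial(47, a) and E binomial(A, c). The last column is the share of trials in which the 4-step arm has more treated children but a lower conditional share:

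| Anaphylaxis, 4- v 5-step | Treated share, 4- v 5-step | Opposite directions |
|---|---|---|
| 20% v 10% | 60% v 75% | 43% |
| 20% v 10% | 60% v 60% | 31% |
| 15% v 10% | 50% v 60% | 20% |

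**How many children.** Expected cases per arm = 47 × a: 2.4 at 5%, 4.7 at 10%, 9.4 at 20%. The chance that at least one arm has no case, which leaves E/A undefined, is 1 − (1 − (1 − a)^47)². At 5%, 0.95^47 = 0.090, giving 17%. At 2%, 0.98^47 = 0.387, giving 62%.

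**Overlap.** Take 6 treated children: 4 respond to one or two doses, and 2 do not improve after two doses and receive a third. As printed, the groups can hold 4 + 2 + 2 = 8 entries for 6 children.

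**The case against.** A reader might infer that the protocol fixes the conditional denominator outright. It does not. The sentence can also be read as children needing epinephrine for anaphylaxis out of the whole arm, and section 2.19 promises an analysis of all randomised participants with no outcome exempted. On that reading the comparison is randomised. The abstract's wording points the other way, however, and section 2.19 is silent on this outcome, so the conditional reading remains the more natural one.

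A reader might also infer that children will be double-counted. Nothing says that the groups are summed. The bullet layout is also unreliable: the fourth bullet is a time window, and the second carries no grade while the third does, so the two may be one severe group split by formatting. Overlap is possible as printed, not certain.

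Nor do the documents support a claim that a ladder with more anaphylaxis would necessarily look safer. The reversal depends on rates the article does not give, and the differences above are far from significant. Changing the denominator does not make rare events informative.

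The strongest mitigation stands. The unconditional anaphylaxis outcome sits directly beside this one, and section 2.15 (Harms) requires adverse events by arm and type for all randomised children. With counts, a reader could rebuild the share per randomised child. The comparison the text most naturally prescribes would still be the unprotected one.

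Exact denominators are often left to an analysis plan, which is not at hand. Here, though, the protocol itself states the outcome, its subgroup, its categories and the between-arm comparison, so the point concerns what is written rather than an omission.

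**Conclusion.** The point holds in limited form. On the most natural reading, the epinephrine outcome compares arms within a group formed after randomisation, under different exposure, and with probably very few children. It can disagree in direction with the comparison per randomised child: in 20% to 43% of simulated trials under the rates tried, all of them assumed. The response groups can overlap as printed. The conclusion rests on reading the denominator as children with anaphylaxis, which the abstract supports but section 2.11.2 does not spell out. The neighbouring outcome and the harms reporting contain the damage, and this is one secondary outcome in a trial that describes itself as a pilot. Minor priority.

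**What to change.** In section 2.11.2:

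1. For the between-arm difference, state that the denominator is all children randomised to each arm, both for any epinephrine use and for each response group.
2. Keep the share among children with anaphylaxis as a descriptive count, without a test, relative risk or number needed to treat.
3. Make the reporting groups mutually exclusive and assign each child to one group by the worst reaction in the observation period.

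If all randomised children are already intended, a line saying so settles the first item. The data are already to be collected and the sample size is unaffected, so the cost is a few lines of outcome wording. The change concerns how the outcome is reported, not how epinephrine is given.

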### Study objective and hypothesis

2.1

The primary aim of this study is to evaluate and compare the efficacy and safety of a 4-step egg ladder (4-EL) and a 5-step egg ladder (5-EL) in children diagnosed with IgE-mediated hen's egg protein allergy.

We hypothesize that the 4-EL, with 6-week intervals, will be sufficient for assessing tolerance to hen's egg proteins in children with IgE-mediated allergy and will result in a greater proportion of children achieving tolerance to raw egg white, confirmed by OFC, compared to the 5-EL, with the same timeframe. This corresponds to an 18-week tolerance acquisition period in the 4-EL group vs. 24 weeks in the 5-EL group.

There is some evidence suggesting that the introduction of baked egg in high-risk children (e.g., those with a history of anaphylaxis) may be both safe and effective (21). However, it remains unclear whether the initial tested dose of baked hen's egg protein in such cases should be lower than, or the same as, that recommended for the general pediatric HEA population.

Therefore, we decided to compare two ladder protocols: the 4-EL, beginning with a muffin containing 1.5 g of hen's egg proteins, and the 5-EL, in which the first two steps consist of muffins containing 0.75 g and 1.5 g of egg proteins, respectively. This approach allows for a reduced allergen load at initial exposure and a longer cumulative exposure to baked hen's egg proteins. Such a strategy may be more appropriate for specific subgroups of patients, particularly those considered to be at higher risk (21).

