### Intervention

2.5

All OFCs will be conducted in accordance with the PRACTical ALLergy (PRACTALL) guidelines (7).

Participants with IgE-mediated HEA will be randomly assigned to one of two groups: the intervention group (4-EL) or the control group (5-EL), with both protocols conducted over 6-week intervals (Table 2 and Supplementary Table S1).

**Table 2 T2:** Comparison of the 4-step (intervention) and 5-step (control) Egg ladder protocols in children with hen's Egg allergy.

Tested product (temperature, heating duration)	The amount of tested product	The amount of whole hen's egg proteins per portion [g]	The amount of hen's egg proteins per 100 g [g]	4- Step Egg Ladder (intervention group)	5- Step Egg Ladder (control group)
MUFFIN 0.75 Temp. 180°C (oven) Heating duration: 30 min (or until center is dry)	1 muffin (approx. 50 g)	0.75	1.5	–	STEP 1
6 weeks of regular dietary exposure to the tolerated quantity of the previously assessed forms					
MUFFIN 1.5 Temp. 180°C (oven) Heating duration: 30 min (or until center is dry)	1 muffin (approx. 50 g)	1.5	3	STEP 1	STEP 2
6 weeks of regular dietary exposure to the tolerated quantity of the previously assessed forms					
PANCAKE Temp. medium heat – approx. 180–190°C (frypan) Heating duration: 2–3 min both sides (until a golden-brown color is achieved)	1 pancake (approx. 84 g)	2.0	2.4	STEP 2	STEP 3
6 weeks of regular dietary exposure to the tolerated quantity of the previously assessed forms					
HARD- BOILED EGG Temp. approx. 100°C; should be added to the water once it reaches a rolling boil Heating duration: 10–12 min	1–3 years: 0.5–1 egg 4–5 years: 1 egg (approx. 50 g)	3.0 per 0.5 egg^a^ 6.0 per egg^a^	12.0	STEP 3	STEP 4
6 weeks of regular dietary exposure to the tolerated quantity of the previously assessed forms					
Almost raw egg: SOFT-BOILED EGG Temp. approx. 100°C; should be added to the water once it reaches a rolling boil Heating duration: 5 min	1–3 years: 0.5–1 egg 4–5 years: 1 egg approx. 50 g)	3.0 per 0.5 egg^a^ 6.0 per egg^a^	12.0	STEP 4	STEP 5
				Duration: 18 weeks	Duration: 24 weeks

a Amounts of hen's egg protein were estimated based on the average content in a medium egg (50 g).

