#### Children with a positive OFC

2.5.3

A positive OFC is defined according to the criteria outlined in the PRACTALL guidelines (Supplementary Table S2) (7). The OFC will be stopped if any red ('Stop') criterion is met, or if two (2) orange (“Observation”) criteria are met.

In the event of a positive OFC result with baked egg (Step 1 of the EL), children will continue with an elimination diet.

A positive OFC result at later stages of the ladder will prevent progression to the next step. At home, the allergen will continue to be administered in the previously tolerated form, with dosage and frequency determined by the research team.

All children with a positive OFC will be excluded from further participation in the study and will receive continued care from the department in accordance with established clinical standards. A repeat OFC will be scheduled within 6–12 months, based on an individual risk assessment of potential adverse events and the attending physician's clinical judgment.

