#### Assessments

2.6.2

Anthropometric data for the child, specifically height and weight, will be collected at study enrollment and at the end of the observation period (either at 18 or 24 weeks, depending on the assigned study arm). Weight (in kilograms) and standing height (in centimeters) will be measured according to standardized protocols.

Prior to the initial OFC and following completion of the egg ladder, the subjective quality of life of all enrolled children and their caregivers will be assessed using the validated, allergy-specific Parent Form of the Food Allergy Quality of Life Questionnaire (FAQLQ-PF) (24). The FAQLQ-PF was developed to measure parental perceptions of health-related quality of life in children aged 0–12 years with food allergies and includes three domains: emotional impact, food anxiety, and social and dietary limitations. In this study, only the age-appropriate versions of the questionnaire for children under 4 years and for those aged 4–6 years will be used, in accordance with the inclusion criteria. These versions contain 14 and 26 items, respectively. A total score ranging from 0 to 6 is calculated as the mean of the subscale scores.

Prior to each OFC, caregivers will assess their level of anxiety specifically related to the OFC using the Subjective Units of Distress Scale (SUDS) (25). On this scale, parents will rate their anxiety from 1 to 100, where 0 represents no anxiety or complete relaxation, and 100 represents extreme anxiety – the highest level of distress ever experienced.

In children with atopic dermatitis, objective skin lesions will be evaluated using the objective SCORAD index (oSCORAD) (26), a validated variant of the Severity Scoring of Atopic Dermatitis (SCORAD). Assessment will be performed prior to the initial OFC and during follow-up examinations at the end of each observation period.

The SCORAD index is a key tool for evaluating the severity of atopic dermatitis and monitoring treatment response It includes both objective measures (extent and intensity of skin lesions), and subjective symptoms (pruritus and sleep disturbance) reported over the preceding 72 h. The oSCORAD omits the subjective component, focusing exclusively on objective clinical findings. The maximum oSCORAD score is 83, with an optional addition of up to 10 points for disfiguring or function-limiting changes in severe cases. Severity categories are defined as follows: mild (<15), moderate (15–40), and severe (>40).

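### After the first OFC, the SUDS comparison between arms covers only families whose child passed every earlier challenge, and the fifth 5-EL rating has no 4-EL counterpart

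*Protocol article*

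**What the plan says.** All places are in the Protocol article.

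- **Contrast (2.11.2).** Secondary outcomes are to be reported as differences between arms. For SUDS this is the mean difference in caregiver anxiety "prior to each OFC, between study groups at each time point".
- **Collection (2.6.2).** Caregivers give the rating before each OFC, and it concerns that OFC. No other SUDS occasion is named.
- **Exit (2.5.3).** "All children with a positive OFC will be excluded from further participation in the study". For the later steps the section adds: "A positive OFC result at later stages of the ladder will prevent progression to the next step". A repeat challenge follows at 6 to 12 months, outside the 18- or 24-week observation period.
- **Schedule (2.1, 2.5, Table 2).** The arms are compared "with both protocols conducted over 6-week intervals". "This corresponds to an 18-week tolerance acquisition period in the 4-EL group vs. 24 weeks in the 5-EL group". Table 2 gives the 4-EL column as "Duration: 18 weeks" with four steps, and 5-EL has five. The first challenge is a 1.5 g muffin in 4-EL and a 0.75 g muffin in 5-EL.
- **Analysis (2.19).** Intention-to-treat on all randomised participants, multiple imputation for missing data, two-sided tests at 5%.
- **Scale (2.6.2).** "parents will rate their anxiety from 1 to 100, where 0 represents no anxiety or complete relaxation".

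**The concern.** The stated contrast presupposes two randomised groups at every rating. The exit rule means that these exist only at the first. At each later OFC the plan compares families still on the ladder, and what it took to stay on differs by arm from the first step. Families whose child had a positive challenge leave the measure, although they are arguably the ones most relevant to an anxiety outcome.

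A gap between arms at a later OFC could then reflect who is left as well as the ladder itself. Read as written, with a test at 5% at each time point, the plan would present such a gap as an effect of allocation. At the fifth OFC there is no second group to compare.

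**Working it through.** **1. The plan's own figure.** 42 / (1 − 0.10) = 46.7, rounded up to 47 per arm and 94 in total, as section 2.9 states. The article gives no SD, effect size or power for SUDS, so there is no SUDS figure to reproduce.

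**2. Rating occasions.** Six-week steps give nominal OFC weeks 0, 6, 12, 18 in 4-EL and 0, 6, 12, 18, 24 in 5-EL. The weeks are nominal because section 2.6.1 lengthens the interval after a break in dosing of more than a week.

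| Nominal week | 4-EL families rated | 5-EL families rated |
|---|---|---|
| 0 | all randomised | all randomised |
| 6 | passed 1.5 g muffin | passed 0.75 g muffin |
| 12 | passed 2 OFCs | passed 2 OFCs |
| 18 | passed 3 OFCs | passed 3 OFCs |
| 24 | no OFC | passed 4 OFCs |

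Of five occasions, one compares the groups as randomised, three compare those remaining, and one has no comparator. The contact six weeks after the ladder (section 2.8) falls near week 24 for 4-EL completers, but it covers tolerance and egg in the diet, with no SUDS stated.

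**3. Does matching by food help?** No. The 0.75 g muffin has no 4-EL counterpart. At the 1.5 g muffin, all 4-EL families would be set against 5-EL families already filtered by one challenge.

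**4. Coverage.** The introduction cites 69% reaching raw-egg tolerance with the ladder. Assume the same pass rate p at each of four challenges: p = 0.69^(1/4) = 0.911. The share still rated is p = 91% at week 6, p² = 83% at week 12 and p³ = 76% at week 18. From 47 families that is 42.8, 39.0 and 35.6. Spreading 69% over five challenges gives 0.69^(1/5) = 0.928, and 43.6, 40.5, 37.6 and 34.9 families at weeks 6, 12, 18 and 24.

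**5. Selection bias at week 6.** Assume that the ladder has no effect on SUDS, SUDS has SD 25, and SUDS and the child's liability to react are bivariate normal with correlation ρ. With pass rate q, the mean SUDS among those who pass shifts by −ρ × SD × φ(z_q)/q.

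- q = 0.85: φ(1.036)/0.85 = 0.274
- q = 0.95: φ(1.645)/0.95 = 0.109
- Difference 0.166. At ρ = 0.2: 0.2 × 25 × 0.166 = 0.8 points. At ρ = 0.4: 0.4 × 25 × 0.166 = 1.7 points. In SD units, 0.03 to 0.07.
- Equal q in both arms: 0.

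With the lower pass rate in 4-EL, this makes the remaining 4-EL families look less anxious.

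**6. Effect on a 5% test.** The standard error at week 6 is 25 × √(1/(47 × 0.85) + 1/(47 × 0.95)) = 5.4 points. A bias of 0.8 to 1.7 points raises the two-sided false-positive rate from 5.0% to about 5.3% to 6.1%.

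**The case against.** The strongest reply is that little is at stake numerically. The calculation above bears this out: under moderate assumptions the false-positive rate hardly moves. This is also one secondary outcome in a trial that section 2.9 calls a pilot, and the primary outcome is untouched. That stands, and it limits the weight of the point.

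Several stronger readings are tempting, and the documents do not support them.

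- **A large bias.** A reader might set the two arms at 70% and 97%, the ends of the baked-egg tolerance range in the introduction, and obtain 2.1 to 4.3 points. That range is a spread across studies. Nothing suggests that two muffins differing in egg dose would separate the arms so far.
- **A collapse in coverage.** Applying 70% to every step would leave 34% of families at week 18 (0.70³). It would also mean that 24% pass four challenges (0.70⁴), which clashes with the 69% that the introduction cites.
- **Every family that saw a reaction leaves.** Section 2.5.3 stops a challenge for one red or two orange criteria, so a child with a single orange sign is not positive on that rule and can continue. Section 2.14 speaks of individual intervals to later steps after an adverse event, but section 2.5.3 is categorical for positive challenges.
- **A misleading fall over time.** The outcome is a difference between groups. No change in SUDS over time is planned.
- **Later comparisons must go.** The rating is about the coming OFC, so a comparison among families still facing one is a legitimate description. The first rating alone captures anticipation of the assigned ladder and not experience of it.

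Two replies carry less. Reading the time points as only those that both arms share would settle the fifth rating, but the text does not say so. Nor do intention-to-treat and imputation in section 2.19 rescue the contrast: anxiety before a challenge that is never held is undefined, not missing.

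**Conclusion.** The point holds on the text alone. Sections 2.5.3, 2.6.2 and 2.11.2 together make every SUDS contrast after the first OFC conditional on having passed earlier challenges, with an arm-specific first filter, and leave the fifth 5-EL rating without a comparator. As written, these contrasts would be reported as differences between randomised arms, which they are not.

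The article does not allow the bias to be sized. On the assumptions shown it is probably modest, and it vanishes in the model if pass rates are equal. The SD, the correlation and the arm-specific pass rates are all assumed, and the coverage figures rest on equal step rates. The case for a change is what the contrast means and how cheaply it can be put right, not a likely false result.

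The mismatch in section 2.6.2 between a scale starting at 1 and an anchor at 0 is clerical and adds no weight.

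**What to change.** In section 2.11.2, restate the SUDS outcome:

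- The only between-arm test is the rating before the first OFC, in all randomised families. Because randomisation precedes that OFC and allocation is known (sections 2.16 and 2.17), say that it measures anticipation of the assigned ladder.
- Report ratings before later OFCs by arm with the number still on the ladder. Differences with confidence intervals may be shown, labelled descriptive and conditional on remaining on the ladder, with no significance claim.
- Report the rating before the fifth OFC for 5-EL only.

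In section 2.6.2, give SUDS one range that includes its own anchor of 0 for no anxiety.

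The cost is a change of wording with no extra data. The downside is fewer between-arm p-values for anxiety.
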